**Fig. 1 Fig1:**
[figure not shown]
Control group: Egocentric block building training

**Fig. 2 Fig2:**
[figure not shown]
Experimental group: Altercentric block building training

#### Data analysis plan

First, we will perform correlation analyses with the pre-test data to examine the associations among visuospatial perspective-taking and ToM and emotion understanding. We hypothesise that there will be positive relationships among preschoolers' visuospatial perspective-taking, ToM, and emotion understanding.

We then will use independent *t*-tests to test the group differences in nonverbal reasoning, inhibitory control, and oral language proficiency and decide if these three variables will be used as covariates in subsequent analysis. Next, we will use repeated measures ANOVAs to examine the post-training improvements in general spatial and mathematics skills in both groups. Previous research has illustrated a positive effect of block-building on preschoolers’ spatial and mathematics skills [83, 84, 86, 87]. We will also examine if the altercentric block-building group improves significantly more than the egocentric block-building group in visuospatial perspective-taking. This will ensure that the altercentric training increases visuospatial perspective-taking that we aim to train.

In the main analysis, we will use repeated measures MANOVAs to determine the post-training changes in understanding mind and emotion across the two groups. We predict that the altercentric block-building group will show greater improvements in ToM and emotion understanding abilities than the egocentric block-building group. Moreover, these improvements will be mediated by the improved visuospatial perspective-taking ability.

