### Theory of mind and language

Language ability has been consistently found to be associated with ToM performance [11, 26–30]. In particular, children’s understanding of mental state vocabulary, such as *think, believe, want, know*, and sentential complements such as “John believes/says it is raining” are linked to their ToM scores [29, 31–33]. There have been two main explanations for this relationship between ToM and language ability [11]. From the perspective of linguistic determinism, researchers argue that language plays a causal role in the development of ToM ability. In other words, children who lack language ability do not achieve ToM [31, 34]. However, there is much controversy over language's specific role in ToM development [26]. The domain-general perspective argues that the majority of the ToM tasks are verbal tasks and thus language is heavily needed in mental state understanding [35, 36].

A number of social-environmental factors have been found to be associated with children’s ToM development, including family size and the number of siblings [37–39], socioeconomic status [2], child’s sociolinguistic awareness [40], mother’s mind-mindedness [41], and mother–child mental state talk [6, 8]. These factors create a social-linguistically enriched environment for children to explore others’ mental stances and perspectives, and as such, children can respond appropriately to social interactions by inhibiting their egocentric perspective. Linguistic scaffolding from elder siblings and parents thus strengthens a child’s capacity to apprehend the abstract mind. From this, we can see that language ability and verbal interaction are essential to developing mind understanding, such as the ability to relate the actions of others to their mental states. This may contribute to the fact that existing ToM training is heavily language-based [42–44]. These language-based ToM training were explicitly designed to teach children mentalistic language and knowledge of inner states through role-playing and story-telling.

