#### Design and procedures

This research proposal has gained approval from the Human Research Ethics Committee of [blinded university]. Written informed consent will be obtained from all participants' parents or legal guardians before the initiation of the study. Parents or legal guardians will be asked to complete a set of questionnaires on family demographics, children's characteristics and executive functioning. Prior to the training, children will first complete a pre-test in a quiet room at the University. Then, children will be randomly assigned to either the (a) egocentric block building or (b) altercentric block building training group. The training period will be six weeks, with a 1.5-h training session per week. The training will be conducted in a child-friendly lab at the University. After the training sessions are completed, the children will be tested with the same battery of measures in the post-test. Upon completion of the training, the participants' parents or legal guardians will receive a report of their child's performance and a gift voucher valued at HKD$200.

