#### Measures

Raven’s Coloured Progressive Matrices (RCPM; [92]) is a non-verbal reasoning test that measures the general cognitive ability of young children aged 4 to 11 years. The RCPM consists of three sub-tests (Set A, AB, B); each subtest has 12 items. For each item, the administrator presents an incomplete design and children are asked to find the missing part of the design from six options to complete the design. The items are arranged in ascending order of difficulty in each subtest. The ascending difficulty levels also apply to the subtests, where Set A is the easiest and Set B the most difficult. A score of one will be given for each correct answer. The maximum possible score is 36, where higher scores indicate a higher level of nonverbal reasoning abilities.

The Bear/Dragon task [93] assesses the executive function of behavioural inhibitory control in young children. This task is a simplified version of the Simon Says task, in which children are required to selectively obey or ignore specific commands according to the rules given by the experimenter. Two stuffed animals, a bear and a dragon, will first be introduced to the children. Then the administrator will instruct the children to follow action commands such as “touch your head” given by the bear, and ignore the ones given by the dragon. After practice, there are 10 randomized trials of the bear and dragon commands. Children’s responses will be assigned a score from 0 to 3 in each dragon trial (0 = full movement, 1 = partial movement, 2 = wrong movement, and 3 = no movement). The maximum possible score is 15, where a higher score indicates better ability in behavioural inhibitory control.

The Hong Kong Test of Preschool Oral Language (Cantonese) (TOPOL-EV; [94]) assesses young children’s oral language abilities in the preschool period (i.e., from 2 years 6 months to 5 years 11 months of age). The expressive vocabulary subtest will be used in this study. The expressive vocabulary subtest consists of 58 items. In each item, the administrator presents one picture and children are required to name the displayed picture. Five categories of vocabulary are tested in this subtest, such as stating the objects or the actions. The items are arranged in ascending order of difficulty. A score of one will be given for each correct answer. The maximum possible score is 58 and higher scores indicate better knowledge of Cantonese expressive vocabulary.

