#### Design, measures and procedures

The procedures will be similar to those in study 1. Written informed consent and information on family demographics, child characteristics, and executive functioning will be obtained from all participants’ parents or legal guardians prior to the initiation of the study. Children will be pre-tested and post-tested with the same battery of measures as those used in study 1. The training period will also be six weeks, with one 1.5-h training session per week. The training will be conducted in a child-friendly lab at the University. Upon completion of the training, the participants' parents or legal guardians will receive a report of their child's performances and a gift voucher valued at HKD$200.

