#### Data analysis plan

The preliminary analyses will be the same as those in study 1. Next, repeated measures MANOVAs will be conducted to compare the effectiveness of the three trainings in improving children’s visuospatial perspective-taking, ToM, and emotion understanding abilities. We predict all of the training in study 2 will increase children’s ToM and emotion understanding. In particular, we hypothesise that the *socialised altercentric block building* training will result in the greatest improvement on the children’s ToM and emotion understanding. We expect the paired dialogic reading to enhance children’s general language ability but not their visuospatial perspective-taking ability. In contrast, we expect that the *parallel altercentric block building* will enhance the children’s visuospatial perspective-taking ability but not their general language ability. We further hypothesise that the *socialised altercentric block-building* training will enhance both visuospatial perspective-taking and language abilities because verbal interaction may strengthen children’s developing ability to simulate the visuospatial experience of others. This finding will reveal whether visuospatial perspective-taking is conducive to developing ToM beyond the contribution of verbal interaction.

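### Inhibitory control is retested after training but used only to choose covariates, so a gain running partly through inhibition could be credited to visuospatial perspective-taking; the task's scoring also gives full marks to a child who never moves

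*Protocol article*

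**What the plan says.** Study 1, Design and procedures, repeats the whole battery: "After the training sessions are completed, the children will be tested with the same battery of measures in the post-test". Bear/Dragon, the measure of behavioural inhibitory control, belongs to that battery (Study 1, Measures).

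The Study 1 Data analysis plan mentions inhibitory control once. Independent t-tests will "test the group differences in nonverbal reasoning, inhibitory control, and oral language proficiency and decide if these three variables will be used as covariates"; no time point is given. The named checks on what training changed are spatial skill, mathematics and visuospatial perspective-taking. For theory of mind (ToM) and emotion understanding, the section predicts that "these improvements will be mediated by the improved visuospatial perspective-taking ability". No other mediator is named.

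Study 2 follows the same pattern: "Children will be pre-tested and post-tested with the same battery of measures as those used in study 1", and "The preliminary analyses will be the same as those in study 1".

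On scoring, Measures states: "Children’s responses will be assigned a score from 0 to 3 in each dragon trial". No movement earns 3, there are 10 bear and dragon trials together, and the maximum is 15.

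**The concern.** The two Study 1 arms are meant to differ in visuospatial perspective-taking. The training descriptions suggest that they may also differ in how often a child must hold back his or her own view. In the control arm the partner sits alongside, so the two frames nearly coincide. In the altercentric arm the partner sits opposite and the target figure is turned by 180°.

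The article's own background makes inhibition a credible rival route. Under Theory of mind and language it says that, in enriched social settings, "children can respond appropriately to social interactions by inhibiting their egocentric perspective". The preceding section on ToM and emotion understanding cites adults' failures to resist their own perspective.

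Randomisation supports a causal statement about the altercentric package. It does not show which ingredient worked. The article aims, in tentative terms, at a statement about visuospatial perspective-taking in particular. Pre-test inhibition as a covariate would not settle this, because the rival route runs through the change in inhibition. The data on that change will have been collected, but no named analysis uses them.

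**Working it through.** **1. Scoring.** Inputs from Measures: maximum 15, up to 3 points per dragon trial, 10 trials in all.

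- Scored dragon trials: 15 / 3 = 5, which reproduces the stated maximum (5 × 3 = 15).
- Unscored bear trials: 10 − 5 = 5.
- A child who obeys every bear command and ignores every dragon command scores 5 × 3 = 15.
- A child who never moves scores 5 × 3 = 15.

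The score cannot tell these two children apart. A child who never moves at pre-test is already at the ceiling, so no gain can show.

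**2. Contrast between the arms.** Study 1, Training activities, lists three seating formats for the altercentric-frame time.

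| Format | Own view to be set aside while building, partner opposite |
|---|---|
| Swap seats and build there | Little: the child sits where the target view is |
| Swap for ten seconds, return, then build | Yes |
| Imagine only | Yes |

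The difference in inhibitory demand therefore arises in two of the three formats. Both arms also begin with the same egocentric-frame time. The share of trials in each format is in Table 1, which is not shown.

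**3. How far the planned mediation protects.** The documents give no effect sizes for this, so every path below is an assumption. The worst case was simulated: training acts on ToM through inhibition only, and the true path from the perspective-taking test (PTT-C) to ToM is zero.

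- n = 79 (the plan's required total), arms of 39 and 40, 4,000 runs per scenario.
- Inhibition gain I = 0.8 × arm + error (SD 1).
- PTT-C gain P = a × arm + c × I + error, with a = 0 or 0.64 (2 × the plan's f = 0.32).
- ToM gain Y = 0.6 × I + 0 × P + error.
- Gains in P and Y have within-arm SD 1. The arm difference in ToM gain is 0.8 × 0.6 = 0.48 SD.
- Mediation is declared when arm → P, and P → Y given arm, are both significant at two-sided 5%. The article names no mediation method, so this rule is also an assumption.

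The table shows the percentage of runs that wrongly declare mediation by PTT-C.

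| c (inhibition → PTT-C) | PTT-C alone, a = 0 | PTT-C alone, a = 0.64 | Inhibition change added, a = 0 | Inhibition change added, a = 0.64 |
|---|---|---|---|---|
| 0 | 0.2 | 4.0 | 0.3 | 4.1 |
| 0.3 | 6.1 | 33.4 | 0.9 | 4.6 |
| 0.5 | 31.4 | 77.1 | 2.0 | 5.0 |
| 0.7 | 67.8 | 97.5 | 3.3 | 4.1 |

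The arm difference in ToM gain is significant in about 56% to 57% of runs. With inhibition change in the model, the inhibition path is found in about 93% to 95% of runs. The simulation treats inhibition as measured without error, so a real Bear/Dragon score would protect less well than the last two columns suggest.

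**The case against.** The strongest reply is that the plan already has a guard. It checks that the altercentric arm gains more on perspective-taking and then expects that gain to mediate the ToM and emotion gains. This stands in part. A reader might infer that any inhibition-driven gain would be credited to perspective-taking. The documents do not support that: with c = 0, false mediation stays at 4% or below. The guard fails only if inhibition also raises PTT-C scores. No section gives that path, though it is plausible, since on the 90° and 180° items the child's view differs from the photographer's.

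A reader might also infer that every altercentric trial requires overriding one's own view. The swap-seats format rules that out.

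Bear/Dragon measures withholding a movement, not suppressing a perspective, and setting aside one's own view is arguably part of perspective-taking itself. Both points stand. They limit what the check can show, above all when it is null.

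The article is condensed, and an unseen analysis plan could add this analysis. That is true, and a reason to treat the point as an improvement. Still, the article does fix the covariate role, the checks and a single mediator.

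On scoring, a practice phase precedes the trials, and the cited source of the task may contain a pass criterion. The frequency of never-moving children is unknown. A reader might infer that such children bias the main result; under randomisation they should fall equally in both arms, so they add noise only.

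**Conclusion.** The point holds as a cheap improvement, not as an error in the plan. Three things are established from the text: inhibition is retested, its change is not used in any named analysis, and the scoring cannot separate a non-responder from a perfect performer (15 of 15 for both). That the arms differ in inhibitory demand is a reasonable inference from two of the three seating formats, not a stated fact.

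The size of any misattribution cannot be derived from the documents. The simulated range of 0.2% to 97.5% shows only how strongly the answer depends on an unknown path from inhibition to PTT-C. Converting the concern into a portion of the planned effect would need an assumed share for the inhibition route, for which the documents give no basis, so no such figure is offered. The randomised comparison of ToM and emotion understanding is unaffected; only the mechanism attached to it is at issue.

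**What to change.** In the Study 1 Data analysis plan:

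1. Add a between-arm comparison of post-test Bear/Dragon adjusted for pre-test, named as a specificity check.
2. Enter the change in Bear/Dragon beside the change in PTT-C in the mediation analysis.
3. State in advance that if inhibition also gains more in the altercentric arm, the result will be attributed to altercentric training (perspective-taking and/or inhibition), not to visuospatial perspective-taking alone.
4. State that Bear/Dragon is a proxy based on motor inhibition, so a null check does not exclude the rival route.
5. Use the bear trials, which are already administered, to flag non-responders under a threshold fixed before the data are seen. Report the Bear/Dragon analyses with and without these children, and keep them in the main ToM and emotion analysis.

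The cost is one or two extra analyses of data already being collected, one scoring rule, and a few Bear/Dragon scores marked invalid. No further testing of children is needed.

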## Research plan and methodology

### Study 1: examining the role of visuospatial perspective-taking in developing theory of mind and emotion understanding

#### Participants

Participants will consist of 96 typically developing Cantonese speaking 4.5-year-olds (48 males; 48 females). The targeted age group is 4.5-year-old children because the ontogenetic development of both ToM and emotion understanding abilities typically emerges at around 4 to 5 years of age [89].

This study will investigate the effect of visuospatial perspective-taking training on children’s ToM and emotion understanding abilities by capitalizing on their mind-understanding differences at this age. Several meta-analyses have reported moderate to large effect sizes for ToM, emotion understanding, and relevant spatial training [43, 90, 91]. The effect size of this study can thus be reasonably estimated as medium-to-large. We used G*Power 3.1 to conduct an a priori power analysis to determine the required sample size. Results indicated that a total sample of 79 participants was required to achieve a power of 0.80 for detecting a medium-to-large effect (*f* = 0.32) at an alpha of 0.05 for a MANOVA (MANOVA: Repeated measures, within-between interaction). To account for a potential attrition rate of 20%, we propose to recruit 48 children per group, thus 96 children in total, via electronic fliers on local internet groups.

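### Baseline t-tests between randomised groups decide which covariates are used, so the model depends on chance imbalance, and the rule does not fit the three arms of Study 2

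*Protocol article*

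**What the plan says.** In the Study 1 data analysis plan, independent t-tests are used "to test the group differences in nonverbal reasoning, inhibitory control, and oral language proficiency" and, from the result, to "decide if these three variables will be used as covariates in subsequent analysis". The later analyses include the repeated-measures MANOVAs on ToM and emotion understanding. The plan gives no threshold for these t-tests and does not say whether they use pre-test or post-test scores, although the same battery is given at both visits.

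Under Design and procedures, the pre-test comes first and then "children will be randomly assigned to either the (a) egocentric block building or (b) altercentric block building training group".

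For Study 2, which has three groups of 40, the data analysis plan says "The preliminary analyses will be the same as those in study 1".

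In the background section on theory of mind and language, the article says: "Language ability has been consistently found to be associated with ToM performance".

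**The concern.** A test of baseline balance after randomisation asks a question whose answer is already known: any difference arose by chance. Whether a covariate is worth including depends on how well it predicts the outcome, and the t-test carries no information on that. A useful predictor that happens to be balanced is dropped, and a useless one that happens to be imbalanced is kept.

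Two things are at stake. First, whether the main result is adjusted, and for what, is settled by the data and not by the plan. Second, precision may be lost in studies whose planned size leaves little slack after the allowed attrition.

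Study 2 adds a practical problem. An independent t-test compares two groups, and the article does not say how the rule works with three.

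**Working it through.** **Inputs from the article.** Three candidate covariates; alpha 0.05, stated for the MANOVA; f = 0.32; 96 children in two groups (Study 1) and 120 in three groups (Study 2); 20% attrition.

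**Assumptions.** The t-tests use pre-test scores and a two-sided 0.05 threshold. The share of variance explained by the covariates (R²) is not in the article, so a range is shown.

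**1. Reproduce the stated sample sizes.** The article reports for Study 1 that "a total sample of 79 participants was required to achieve a power of 0.80", "at an alpha of 0.05 for a MANOVA" with a within-between interaction. With two time points and k groups, the test is F with df1 = k − 1, df2 = N − k and noncentrality λ = f²N.
- Study 1, k = 2, N = 79: λ = 0.1024 × 79 = 8.09, power 0.802. N = 78 gives 0.797. The stated 79 is reproduced.
- Study 2, k = 3, N = 98: λ = 0.1024 × 98 = 10.04, power 0.804. N = 97 gives 0.799. The stated 98 is reproduced.

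**2. How often the rule drops covariates in Study 1.**
- One covariate: dropped with probability 1 − 0.05 = 0.95.
- All three, if independent: 0.95³ = 0.857. At least one is kept with probability 1 − 0.857 = 0.143.
- By simulation with 48 per group, at least one is kept in 14.4%, 13.2% and 12.5% of trials when the covariates intercorrelate at 0, 0.3 and 0.5. Correlation makes dropping all three slightly more likely.

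**3. What always adjusting would gain.** Completers in Study 1: 96 × 0.80 = 76.8, rounded down to 76. With three covariates, λ = f²N/(1 − R²) and df2 = 76 − 2 − 3 = 71. Because the planned interaction with two time points is a test on pre-post change, R² here is the share of the variance of change.

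| Strategy | R² for change (assumed) | λ | Power |
|---|---|---|---|
| No covariates (df2 = 74) | – | 7.78 | 0.786 |
| Always adjust | 0 | 7.78 | 0.786 |
| Always adjust | 0.05 | 8.19 | 0.806 |
| Always adjust | 0.10 | 8.65 | 0.827 |
| Always adjust | 0.20 | 9.73 | 0.868 |
| Always adjust | 0.30 | 11.12 | 0.908 |

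In the R² = 0 row, the three lost degrees of freedom cost less than 0.001 of power (0.7862 to 0.7858).

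**4. The plan's rule against fixed adjustment.** Simulation with 40 per group, d = 2f = 0.64 and covariate intercorrelation 0.3 (5,000 replicates for power, 10,000 for type I error):

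| R² | Power, plan's rule | Power, always adjust | Type I error, plan's rule | Type I error, always adjust |
|---|---|---|---|---|
| 0 | 0.81 | 0.80 | 0.048 | 0.050 |
| 0.1 | 0.81 | 0.84 | 0.046 | 0.052 |
| 0.2 | 0.82 | 0.87 | 0.044 | 0.048 |
| 0.3 | 0.81 | 0.91 | 0.038 | 0.048 |

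The plan's rule behaves almost like no adjustment for power, and its type I error falls below 0.05 as R² rises.

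**5. Study 2.** Expected completers are 120 × 0.80 = 96, where unadjusted power is 0.795. A two-sample t-test does not compare three groups at once, and the article does not say what replaces it or what follows if only one pair of groups differs.

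**The case against.** The strongest objection concerns the size of the gain. The article supports an association of language with ToM performance, not with change over six weeks. Stable differences between children are already removed by analysing change. If a covariate correlates equally with pre and post scores of equal variance, its R² for change is zero. As an illustration, take unit SDs and an assumed pre-post correlation of 0.6, so change has variance 2 − 1.2 = 0.8. Correlations of 0.5 with pre and 0.6 with post then give R² = 0.1²/0.8, about 1%. Reaching 10% needs the correlation to shift by √(0.1 × 0.8) = 0.28 between visits. This stands: the upper rows of the power range may be out of reach, and lost power is possible, not shown.

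Four stronger readings are tempting, and the document does not support them.
- **Inflated false positives.** Choosing a model from the data might suggest this. The simulation points the other way: the test is slightly conservative.
- **All three variables as known strong predictors of ToM.** The article makes the case for language only.
- **A stated significance threshold.** None is given for the t-tests. Significance at 0.05 is the natural reading, but it is an assumption.
- **Nine pairwise t-tests in Study 2.** Three pairs by three variables would show at least one significant pair in about 28% to 32% of trials, but the article never describes that procedure. A one-way ANOVA per variable is the obvious counterpart and would bring the figure back to about 14%.

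It can also be said that an article leaves detail to a fuller plan. That covers the three-arm mechanics in part. It does not cover the selection rule itself, which the article states.

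**Conclusion.** The point holds as a matter of efficiency and clarity. The article fixes a covariate rule that looks at chance imbalance and ignores predictive value. At an assumed two-sided 0.05 it drops each covariate about 95% of the time and, if they are independent, all three about 86% of the time. The main model is therefore data-dependent, and the rule cannot be carried out in Study 2 as written.

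The cost in power runs from nothing (R² for change near 0) to about 0.12 at 76 completers (0.786 against 0.908 at R² = 0.3). The low end is plausible. Even R² = 0.05 would bring Study 1 back above 0.80 at the planned attrition. No bias or excess of false positives is shown. The existence of the rule is certain; the size of its effect rests on the assumed threshold and on R² values that the article does not give.

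**What to change.** Delete the t-test step as the way of choosing covariates. In its place, state for both studies that the main ToM and emotion-understanding models include named pre-test covariates whatever the baseline differences: at least TOPOL-EV, and preferably also RCPM and Bear/Dragon.

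- Mean-centre the covariates. In a repeated-measures model they also enter through covariate-by-time terms, and uncentred values would change the test of the time effect, which matters for the Study 2 prediction that all trainings improve ToM and emotion understanding.
- Use pre-test values only. Study 2 expects language to change in two of its arms, so adjusting for post-test language would adjust for an effect of training.
- Report baseline values by group descriptively, without tests.

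This takes a sentence or two in each data analysis plan and no new data. The statistical cost is three degrees of freedom, under 0.001 of power if the covariates explain nothing.

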### Study 2: Comparing the roles of visuospatial perspective-taking and verbal interaction in developing theory of mind and emotion understanding

#### Participants

This study will compare the effects of three different training methods on the development of mind and emotion understanding in preschool children. Participants will consist of 120 typically developing Cantonese-speaking 4.5-year-olds (60 males; 60 females), with 40 children in each training group. We used G*Power 3.1 to conduct an a priori power analysis to determine the required sample size. Results indicated that a total sample of 98 participants was required to achieve a power of 0.80 for detecting a medium-to-large effect (*f* = 0.32) at an alpha of 0.05 for a MANOVA (MANOVA: Repeated measures, within-between interaction). To account for a potential attrition rate of 20%, we propose to recruit 40 children per group, thus 120 children in total, via electronic fliers on local internet groups.

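### Free improvement: the main between-group test compares raw pre-post change, when adjusting the post-test for the pre-test already collected would be more precise

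*Protocol article*

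**What the plan says.** The Study 1 data analysis plan fixes the main analysis: "In the main analysis, we will use repeated measures MANOVAs to determine the post-training changes in understanding mind and emotion across the two groups". The Study 2 data analysis plan repeats the method: "repeated measures MANOVAs will be conducted to compare the effectiveness of the three trainings". The Participants sections of both studies name the effect that was powered, "MANOVA: Repeated measures, within-between interaction", with the calculation made "for detecting a medium-to-large effect (*f* = 0.32) at an alpha of 0.05".

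There are two measurement occasions, a pre-test and a post-test with the same battery. In Study 1 (Design and procedures) children complete the pre-test and are then randomised. Study 2 (Design, measures and procedures) describes its procedures as similar and does not restate the order.

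The Study 1 analysis plan considers three covariates: nonverbal reasoning, inhibitory control and oral language. Whether they enter depends on t-tests between groups. The pre-test theory-of-mind (ToM) and emotion scores are not named as covariates for their own post-test scores.

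**The concern.** With two occasions, the group-by-time interaction is a between-group comparison of post-test minus pre-test. That subtracts the whole baseline score, as if the post-test followed the pre-test with a slope of 1. When the pre-post correlation is below 1 and the variances are equal, the slope is below 1. Full subtraction then over-corrects and adds noise. The change score is also negatively correlated with baseline, so a chance baseline difference between groups carries into the estimate.

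Because the pre-test precedes randomisation, a regression of the post-test on group and pre-test estimates the same training effect with smaller variance. What is at stake is precision in two small studies, both of which fall slightly short of their calculated size if the assumed attrition occurs.

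**Working it through.** **Inputs from the protocol article.** f = 0.32, alpha 0.05, power 0.80. Study 1: "a total sample of 79 participants was required to achieve a power of 0.80"; "To account for a potential attrition rate of 20%, we propose to recruit 48 children per group, thus 96 children in total". Study 2: "a total sample of 98 participants was required to achieve a power of 0.80"; 120 recruited, 40 per group, with the same 20% attrition. Two occasions. No pre-post correlation, reliability or standard deviation is given for either outcome.

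**Step 1. Reproduce the plan's own figures.** Take the group-by-time test on change for k groups as an F test with df1 = k-1, df2 = N-k and noncentrality λ = f²N, where f² = 0.1024.
- Study 1, k = 2: N = 79 gives λ = 8.09 and power 0.802; N = 78 gives 0.797. The smallest N is 79, as stated.
- Study 2, k = 3: N = 98 gives λ = 10.04 and power 0.804; N = 97 gives 0.799. The smallest N is 98, as stated.

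Reading f on the raw-score scale with correlation 0.5 would give 22 and 27. The stated sizes therefore fit a test on change, one outcome at a time (df1 = 1 in Study 1).

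**Step 2. Compare the two analyses.** Let the pre and post variances both be σ², with correlation r.
- Change score: variance 2σ²(1-r).
- Post-test adjusted for pre-test: variance σ²(1-r²).
- Ratio: (1-r²)/[2(1-r)] = (1+r)/2. The reduction is 1-(1+r)/2 = (1-r)/2.

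| r (assumed) | Variance ratio | Variance reduction | SE ratio |
|---|---|---|---|
| 0.2 | 0.60 | 40% | 0.775 |
| 0.5 | 0.75 | 25% | 0.866 |
| 0.6 | 0.80 | 20% | 0.894 |
| 0.7 | 0.85 | 15% | 0.922 |
| 0.8 | 0.90 | 10% | 0.949 |
| 0.9 | 0.95 | 5% | 0.975 |

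The standard error is therefore about 8-13% smaller at r = 0.7-0.5. A simulation with 40 children per group gave variance ratios of 0.755 at r = 0.5 and 0.865 at r = 0.7, so the finite-sample gain is slightly below theory.

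**Step 3. Translate into power.** With 20% loss, 96 × 0.8 = 76.8 (about 76) and 120 × 0.8 = 96 children remain. Divide λ by (1+r)/2 and spend one error degree of freedom on the covariate.

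| | Change | r = 0.7 | r = 0.6 | r = 0.5 |
|---|---|---|---|---|
| Study 1, N = 76 | 0.79 | 0.85 | 0.87 | 0.89 |
| Study 2, N = 96 | 0.79 | 0.86 | 0.88 | 0.90 |

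For 0.80 power, the required totals at r = 0.7, 0.6 and 0.5 become 68, 64 and 60 in Study 1 (instead of 79), and 84, 79 and 74 in Study 2 (instead of 98).

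**The case against.** The strongest reply is that nothing here is an error. The comparison of change is unbiased under randomisation, the analysis and the sample size name the same test, and both stated totals reproduce. That stands: the planned power does not depend on any change, and a reader who infers that the main analysis is invalid or mis-powered by this choice would be wrong.

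A reader might also take the 15-25% loss as a property of this trial. The documents do not support that. It is the result for an assumed r of 0.7-0.5 with equal variances, and it is on the variance scale.

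Nor does baseline adjustment cure ceiling effects on the short scales (stated maximum 5 for both outcomes). A ceiling on the post-test remains under either model, the documents do not show that children will be near it, and bounded scores make equal variances less certain. Upward regression of low scorers is the same in expectation in both randomised arms and does not bias the contrast.

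The power figures treat one outcome at a time and children as independent, whereas the plan uses MANOVA and trains children in pairs. They are illustrations.

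Finally, the Study 2 analysis plan predicts that all three trainings will raise ToM and emotion understanding. That is an improvement over time within groups, which a between-group covariance analysis does not test. This objection stands, and it rules out replacing the repeated measures analysis outright.

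**Conclusion.** The point holds as a free improvement in efficiency. The planned between-group test is valid and consistently powered, but it uses the pre-test less well than it could. The gain is (1-r)/2 of the variance: 5% to 40% for r from 0.9 to 0.2. Its direction is certain in large samples for any r below 1 with equal variances; its size is not known, because the documents give no r. At r = 0.7-0.5 it would more than make up the small shortfall in completers (76 against 79, and 96 against 98), on a one-outcome calculation with independent children.

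The argument needs the pre-test to precede randomisation. This is explicit for Study 1 and rests on the word similar for Study 2.

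**What to change.** In both data analysis plans, make the primary between-group test of ToM and emotion understanding a model of the post-test score on training group and that outcome's own pre-test score: ANCOVA for each outcome, or MANCOVA for the two jointly. Include the pre-test regardless of any baseline t-test. Report the adjusted group difference with its 95% interval.

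Keep the repeated measures analysis for the predicted within-group improvement over time, and as a sensitivity analysis for the group comparison. State in Study 2 that randomisation follows the pre-test, if it does.

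The cost is wording in the two analysis sections. No further data or children are needed, and the stated sample sizes can stand.
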